|                                       | 4. Any incompatibility or allergy to the administration of sarilumab or corticosteroids.                                                                                                                                                                                                                                                                                                                                                                                                                                                                                                                                                                                                                                                                                                                                                                                                                                                                                                                                                                                                                                                                                                                     |
| Study drug dose                | 
Sarilumab will be administered intravenously following this posology:
 
-Patients <75kg body weight: single 200mg SARILUMAB dose (1 single-dose pre-filled syringe containing 200 mg sarilumab in 1.14 ml solution (175 mg/ml) added to 100 mL 0.9% sodium chloride for a 1-hour intravenous infusion).
 
-Patients ≥75kg body weight: single 400mg SARILUMAB dose (2 single-dose pre-filled syringes, each containing 200 mg sarilumab in 1.14 ml solution (175 mg/ml) added to 100 mL 0.9% sodium chloride for a 1-hour intravenous infusion).
 
In addition, all study participants will receive treatment with corticosteroids intravenously following this posology: Methylprednisolone 1mg/kg/day (or corticosteroid dose equivalents) for at least 3 days
 
Sarilumab plus corticosteroids or corticosteroids alone will be given in add-on to SOC medication. SOC medication will be based on local clinical practice recommendations.
                                                                                                                                                                                                                                 |
| Duration of study              | The observation period will be from randomization until 28 days after randomisation, hospital discharge, ICU admission or death, whichever occurs first.                                                                                                                                                                                                                                                                                                                                                                                                                                                                                                                                                                                                                                                                                                                                                                                                                                                                                                                                                                                                                                                     |
| General design and methodology | 
A multi-center, randomized, clinical trial with two arms to study the efficacy and safety of early treatment with sarilumab plus SOC compared to standard of care (SOC) in patients with COVID-19 pneumonia (BCRSS score 1).
 
Experimental arm: Sarilumab + methylprednisolone (or equivalent doses) plus SOC for COVID-19
 
Control arm: Methylprednisolone (or equivalent doses) plus SOC for COVID-19.
 
Randomization will be 1:1 to any of the treatment groups and will be stratified per center.
 
Methylprednisolone 1mg/kg/day (or corticosteroid dose equivalents) for at least 3 days.
 
SOC includes any drugs that are being used in clinical practice (e.g. lopinavir/ritonavir; hydroxy/chloroquine, and other than those used as part of another clinical trial) according to each site local protocol.
 
Patients will be followed up to four weeks after randomization.
 
Patients randomized to the control arm (CS + SOC group without sarilumab) progressing to severe respiratory failure fulfilling criteria for treatment with anti-IL6 inhibitors according to clinical practice guidelines, as defined by the presence of Brescia-COVID
 |

|                                         |                                                                                                                                                                                                                                                                                                                                                                                                                                                                                                                                                                                                                                                                                                                                                                                                                                                                                                                                                                                                                                                                                                                                                                                                                                                                                                                |
|-----------------------------------------|----------------------------------------------------------------------------------------------------------------------------------------------------------------------------------------------------------------------------------------------------------------------------------------------------------------------------------------------------------------------------------------------------------------------------------------------------------------------------------------------------------------------------------------------------------------------------------------------------------------------------------------------------------------------------------------------------------------------------------------------------------------------------------------------------------------------------------------------------------------------------------------------------------------------------------------------------------------------------------------------------------------------------------------------------------------------------------------------------------------------------------------------------------------------------------------------------------------------------------------------------------------------------------------------------------------|
|                                         | 
Scale 2-3 plus inflammatory markers, will be offered the option to be rescued with sarilumab at the same doses and be included in an open-label follow-up phase. This group of patients will be followed up for two additional weeks following sarilumab administration.
 
The results of the study will also be compared with an external cohort of matched patients that did not receive IL-6 inhibitors. This cohort of patients is already being collected as part of an academic multicenter, national, prospective observational cohorts Study being conducted by the same investigation team. This will provide further contextualization to our results and facilitate interpretation.
                                                                                                                                                                                                                                                                                                                                                                                                                                                                                                                                                                                                     |
| Primary measure and endpoint:    | 
The primary endpoint is the proportion of patients progressing to severe respiratory failure (Brescia-COVID Scale <math>\geq 2</math>), ICU admission, or death.
                                                                                                                                                                                                                                                                                                                                                                                                                                                                                                                                                                                                                                                                                                                                                                                                                                                                                                                                                                                                                                                                                                                                        |
| Secondary measures and endpoints | 
Time to progression to severe respiratory failure (Brescia-COVID <math>\geq 2</math>)
 
Time to reduction of supplemental oxygen requirements
 
Time to non-invasive or invasive mechanical ventilation.
 
Rate of hospital discharge and duration of hospitalization
 
Mortality rate and survival time
 
Rate of ICU admission
 
Proportion of patients with at least 1 point progression in the 7-point ordinal scale
 
Ordinal scale:
 
 
1) Not hospitalized, no limitations on activities.
 
2) Not hospitalized, limitation on activities.
 
3) Hospitalized, not requiring supplemental oxygen.
 
4) Hospitalized, requiring supplemental oxygen.
 
5) Hospitalized, on non-invasive ventilation or high flow oxygen devices or oxygen mask with reservoir bag.
 
6) Hospitalized, on invasive mechanical ventilation or ECMO.
 
7) Death.
 
 
Changes from baseline to day 15th in serum levels of inflammatory cytokines.
 
Proportion of patients showing more than >1 organ failure, e.g. cardiovascular, liver and kidney failure
 
Safety and tolerability – Adverse events
 |

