of the primary analysis and be rescued according to local treatment protocols, which may include tocilizumab. Patients in the control group (SOC group without sarilumab) progressing to Brescia-COVID 2-3 plus inflammatory markers, will be given the option to be rescued with sarilumab at the same doses and, in that case, be included in an open-label phase and be followed up for two additional weeks (with visits at 3, 7 and 15 days after sarilumab rescue administration).

A final follow-up visit will be conducted for all patients at D29 from randomization, regardless of initial treatment assignment.

Figure 1 – Graphical study design

[figure not shown]

Figure 2 – Graphical study design OPEN-LABEL PHASE

[figure not shown]

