### ***Dosing and Administration***

Experimental group: Patients in the treatment arm will receive sarilumab plus corticosteroids on top of SOC medication. Sarilumab will be administered intravenously as a single dose following this posology:

- Patients <75kg body weight: single 200mg SARILUMAB dose (1 single-dose pre-filled syringe containing 200 mg sarilumab in 1.14 ml solution (175 mg/ml) added to 100 mL 0.9% sodium chloride for a 1-hour intravenous infusion).
- Patients ≥75kg body weight: single 400mg SARILUMAB dose (2 single-dose pre-filled syringes, each containing 200 mg sarilumab in 1.14 ml solution (175 mg/ml) added to 100 mL 0.9% sodium chloride for a 1-hour intravenous infusion).
- Corticosteroids will be administered intravenously following this posology: Methylprednisolone 1mg/kg/day (or corticosteroid dose equivalents) for at least 3 days

**Control group:** Patients in the control group will receive corticosteroids on top of SOC medication.

Corticosteroid: will be administered intravenously following this posology: Methylprednisolone 1mg/kg/day (or corticosteroid dose equivalents).

SOC: All patients will continue background SOC according to local clinical practice protocols and be followed up until disease progression, patient withdrawal, ICU admission, hospital discharge, loss of follow up, or death.

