#### *Efficacy assessments: follow up visits*

Clinical follow-up visits will be performed at 3, 5, and 15 days after treatment randomisation. Patients in SOC group without sarilumab progressing to severe respiratory failure fulfilling criteria for treatment with anti-IL6 inhibitors according to clinical practice guidelines, as defined by the presence of Brescia-COVID 2-3 plus inflammatory markers, will be rescued with sarilumab at the same doses and be included in an open-label phase. This group of patients will be followed up by two additional weeks after receiving sarilumab as rescue medication (days 3, 5 and 15 following sarilumab administration).

Patients randomly assigned to sarilumab therapy at baseline progressing to Brescia-COVID 2-3 will be rescued according to local clinical practice protocols.

For all patients a final follow-up visit is planned at D28 from randomization, regardless of the initial treatment assigned.

The following outcomes should be assessed:

- Hospitalization.
- ICU admission
- Hospital discharge
- Oxygen requirements.
  - Oxygen mask with reservoir bag.

- Non-invasive mechanical ventilation (via mask) or high flow oxygen nasal tubes
  - Mechanical ventilator requirement (via endotracheal tube or tracheostomy tub).
  - ECMO requirement.
- Ordinal scale score:
  1. Not hospitalized, no limitations on activities.
  2. Not hospitalized, limitation on activities.
  3. Hospitalized, not requiring supplemental oxygen.
  4. Hospitalized, requiring supplemental oxygen.
  5. Hospitalized, on non-invasive ventilation or high flow oxygen devices or oxygen mask with reservoir bag.
  6. Hospitalized, on invasive mechanical ventilation or ECMO.
  7. Death.
- PaO2/FiO2 Index or SpO2/FiO2 Index.
- Temperature °C
- Chest radiography (at least one during the follow-up period, recommended between D3-5, unless medically indicated any other day as part of the routine care)
- Laboratory disease parameters (CRP, d-dimer, IL-6, LDH, lymphocyte counts, ferritin, plus any routing laboratory determinations usually performed by the patients's physicians)
- Death.
- Concomitant medications
- Brescia-COVID score

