### *Secondary endpoints*

1. Time to progression to severe respiratory failure
2. Time to reduction of supplemental oxygen requirements
3. Time to non-invasive or invasive ventilation.
4. Proportion of patients with at least 1 point progression in the 7-point ordinal scale from randomization up to day 15

Ordinal scale:

1. Not hospitalized, no limitations on activities.
  2. Not hospitalized, limitation on activities.
  3. Hospitalized, not requiring supplemental oxygen.
  4. Hospitalized, requiring supplemental oxygen.
  5. Hospitalized, on non-invasive ventilation or high flow oxygen devices or oxygen mask with reservoir bag.
  6. Hospitalized, on invasive mechanical ventilation or ECMO.
  7. Death.
5. Rate of hospital discharge
  6. Duration of hospitalization
  7. Mortality rate and survival time.
  8. Rate of ICU admission
  9. Changes in serum levels of inflammatory cytokines.
  10. Proportion of patients showing more than >1 organ failure, e.g. cardiovascular, liver and kidney failure
  11. Safety and tolerability – Adverse event: The occurrence of treatment adverse events (AEs), serious AEs (SAEs), and laboratory abnormalities in the following, but not limited to, parameters: acute phase reactants CRP and ESR, complete blood count (including ANC and platelets), liver enzymes (ALT, AST and AP), and lipid levels, (time frame: up to day 15)

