#### *Survival endpoints*

The survival function as well as the median [95% confidence interval -95%CI-] time to event will be estimated by means of the Kaplan-Meier method. Group comparisons will be done using the (stratified) log-rank test and the (stratified) hazard ratios -HR- (95%CI) were taken from the Cox model.

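### Two passages end follow-up at discharge, ICU admission or progression, while the visit plan and schedules follow every patient to day 28 or 29

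*Protocol*

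**What the plan says.** Passages that end follow-up early:

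- Synopsis, Duration of study: "The observation period will be from randomization until 28 days after randomisation, hospital discharge, ICU admission or death, whichever occurs first".
- Section 7, Dosing and Administration, SOC paragraph: all patients continue background SOC and are to "be followed up until disease progression, patient withdrawal, ICU admission, hospital discharge, loss of follow up, or death".
- Section 5 uses a similar phrase for the open-label rescue phase, which runs 15 days unless discharge, ICU admission or death comes first.

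Passages that follow everyone to the end:

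- Synopsis, General design: "Patients will be followed up to four weeks after randomization".
- Section 5: "A final follow-up visit will be conducted for all patients at D29 from randomization, regardless of initial treatment assignment".
- Section 8, Efficacy assessments: "For all patients a final follow-up visit is planned at D28 from randomization, regardless of the initial treatment assigned". Discharged patients are to be telephoned.
- Section 8, Follow-up period, refers to a scheduled 28-day follow-up for each patient. The Calendar of Evaluation collects adverse events for up to 28 days, and Table 1 takes safety through day 29.
- Tables 2 and 3 mark mortality and AE/SAE reporting at the day-28 contact. Table 3 does so for control patients who have already progressed and been rescued.

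The endpoints that depend on this include "Mortality rate and survival time" and time to non-invasive or invasive ventilation. For survival endpoints, median "time to event will be estimated by means of the Kaplan-Meier method", with log-rank tests and Cox models.

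**The concern.** The two sets of passages cannot both be followed. Under the first, a patient who enters the ICU, goes home or (by the Dosing and Administration text) progresses is no longer observed. Deaths in this population come mostly after worsening, so the shorter rules would remove vital status where it carries most information. The arms would also lose data unequally if the drug works, since the protocol assumes 25% against 10% for the primary composite.

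Four things are at stake: mortality, survival time, time to ventilation, and safety. In any survival analysis of such data, patients would leave the risk set because they had worsened or because they had recovered, and either kind of censoring is informative. A statistical analysis plan cannot repair this afterwards, because it cannot restore data that sites stopped collecting. Pharmacovigilance would not reliably fill the gap either: section 9 does not require deaths to be reported as SAEs and relies on the CRF to record them.

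**Working it through.** **1. What each rule loses**

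| Event | Synopsis, Duration of study | Dosing and Administration | Visit plan and Tables 2–3 |
|---|---|---|---|
| Progression on the ward | observation continues | follow-up ends | continues to day 28/29 |
| ICU admission | ends | ends | continues |
| Discharge | ends | ends | continues, by telephone |

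ICU admission and discharge end follow-up in both early-stopping passages; progression does so only in the second. The passages that follow everyone also differ among themselves, with day 28 in most and day 29 in section 5 and Table 1.

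**2. The plan's own figure**

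The sample size reproduces. With 25% vs 10%, two-sided 5%, 80% power and pooled variance:

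n = [1.960·√(2·0.175·0.825) + 0.842·√(0.25·0.75 + 0.10·0.90)]² / 0.15² = 99.5, so 100 per arm (power 80.2%).

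The follow-up conflict does not alter it.

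**3. Illustration for mortality**

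From the protocol: p = 25% and 10%. These are the composite rates, used here as progression rates, so they are upper limits for progression alone.

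Assumed:

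- case fatality after progression f = 20%, 30% or 40%;
- mortality of 0.5% without progression;
- a share b = 0, 10% or 30% of deaths among progressors with no earlier recorded progression or ICU admission;
- uniform timing: progression on day 0.5–10, death 1–17 days later, other deaths on day 1–27, discharge of non-progressors on day 4–14.

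Mortality with full follow-up = p·f + (1−p)·0.005. For f = 30% this is 0.25·0.30 + 0.75·0.005 = 7.9% in control and 0.10·0.30 + 0.90·0.005 = 3.45% on sarilumab.

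Deaths recorded if follow-up stops at progression or discharge = p·f·b + (1−p)·0.005·q. Here q = (9−1)/26 = 0.31 is the chance that a death without progression precedes discharge (mean discharge day 9). For control with f = 30% this gives 0.1% (b = 0) to 2.4% (b = 30%), against 7.9%.

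Kaplan-Meier 28-day mortality under the stopping rule, from a simulation of 200,000 patients per scenario:

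| p | f | Full follow-up (formula) | b = 0 | b = 10% | b = 30% |
|---|---|---|---|---|---|
| 25% | 20% | 5.4% | 0.24% | 1.05% | 2.50% |
| 25% | 30% | 7.9% | 0.23% | 1.29% | 3.62% |
| 25% | 40% | 10.4% | 0.20% | 1.77% | 4.73% |
| 10% | 20% | 2.45% | 0.24% | 0.50% | 1.06% |
| 10% | 30% | 3.45% | 0.23% | 0.66% | 1.47% |
| 10% | 40% | 4.45% | 0.25% | 0.81% | 1.89% |

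Simulated mortality with full follow-up was 5.3–10.4% at p = 25% and 2.4–4.5% at p = 10%. The share of control mortality missed runs from 1 − 2.50/5.37 = 53% to 1 − 0.20/10.23 = 98%. The difference between arms shrinks from 2.9–6.0 points (5.34 − 2.43 to 10.43 − 4.44) to between −0.05 and 2.8 points (0.20 − 0.25 to 4.73 − 1.89).

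This is the stricter rule of Dosing and Administration. The Synopsis rule still observes patients who progress but stay on the ward, so its loss would be smaller. The protocol gives no ICU admission rate from which to size it.

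**4. Primary composite**

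Progression, ICU admission and death are all failures. A patient whose follow-up ends at progression or ICU admission has already been counted. Only events after discharge could be missed.

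**The case against.** The strongest reply is that the text leans clearly towards full follow-up. Section 5, the visit section, the telephone contact after discharge, the adverse-event window and both schedules all point that way. The Dosing and Administration sentence sits in a paragraph about background therapy, and the Synopsis row could be read as describing the inpatient period only. The withdrawal section also wants outcome data kept whenever possible. All of this stands as evidence of intent. It does not settle the matter, because no passage is given precedence and a site could apply either rule in good faith.

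Four further points limit what can be claimed.

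- **Censoring.** A reader might infer that the protocol censors patients at ICU admission or progression. It does not say so: the Survival endpoints section states no censoring rule, and a detailed plan is promised. The Kaplan-Meier effect is conditional on sites following the shorter rules. Methods for competing events are choices that the analysis plan may settle, so their absence here is not an error.
- **Horizon.** A reader might infer that a 28-day mortality endpoint is lost. Table 1 names 15-day mortality and the Secondary endpoints list gives no window. Deaths after ICU admission would be lost at either horizon.
- **Missing data.** That section, though garbled, appears to count missing binary efficacy outcomes as failures. For a binary mortality rate, lost deaths would then not simply vanish. But patients discharged alive would be counted as failures too, so the bias changes direction and is not removed. Survival time is not covered.
- **Event rates.** It is tempting to use 25% and 10% as ICU or death rates to size the distortion of recovery endpoints. They are rates for the wider composite, so ICU admission and death can only be equally or less frequent.

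**Conclusion.** The contradiction is in the text and is not reconciled. Applied as written, the Synopsis row and the Dosing and Administration sentence would leave deaths and serious adverse events after ICU admission or discharge unobserved, and the second also those after progression. Mortality, survival time, time to ventilation and safety would be biased.

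The size depends on how many sites follow which rule, which the document cannot tell. The illustration, with more than half of control mortality missed, is close to a worst case: every site stops at progression or discharge, the composite rates stand in for progression, and case fatality and timing are assumed.

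A reader might conclude that the primary analysis is compromised. The documents do not support that, because progression and ICU admission are themselves failures; at most, events after discharge could be lost. The sample size is unaffected. The point deserves correction because secondary and safety results are exposed and the remedy is cheap.

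**What to change.** Reword the Synopsis Duration of study row, the SOC paragraph under Dosing and Administration, and the open-label phrase in section 5 so that they carry one statement, for example: *All randomised patients are followed for vital status and serious adverse events to the scheduled final visit, regardless of discharge, progression, ICU admission or rescue. None of these events ends follow-up or censors survival time.* Vital status should be named separately because deaths need not be reported as SAEs. Use a single day number, 28 or 29, for the final visit and the safety window throughout.

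The cost is a wording amendment. The final contact is already scheduled for everyone with clinical data, mortality and AE/SAE collection, and discharged patients are already telephoned. Ventilator requirement is scheduled only to day 15 in Table 2, and this change does not need it at day 28; it needs only that the existing visits continue after ICU admission. The sample size and the named survival methods stay as they are.
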